## Abstract

**Introduction:**

There is significant potential to improve outcomes for patients with lung cancer in terms of quality of life and survival. There is some evidence that prehabilitation can help, but, to date, this has only been tested in surgical populations, despite 70%–80% of patients with lung cancer in the UK receiving non-surgical treatment. The physiological and psychological benefits of prehabilitation seen in surgical patients could be extrapolated to those receiving non-surgical treatment, particularly in such a poor prognosis group. With patients and healthcare professionals, we have co-designed a personalised and evidence-based prehabilitation programme. This draws on a conceptual framework that aligns with patient values and needs as well as functional goals. We aim to investigate whether this programme is feasible to implement and evaluate in clinical practice.

**Methods and analysis:**

An open-label, single-group feasibility study incorporating quantitative assessments, a qualitative free text questionnaire and reflective field notes. Thirty participants will be recruited over an eight-month period from a single London teaching hospital. All recruited participants will receive a personalised prehabilitation programme during their oncological treatment. This includes a one-hour face-to-face appointment prior to, at week three and at week six of their treatment regimen as well as a weekly telephone call. Interventions including nutrition, physical activity and psychological well-being are stratified according to a patient’s priorities, level of readiness and expressed needs. The primary outcome will be feasibility of the personalised prehabilitation programme in clinical practice by investigating areas of uncertainty regarding patient recruitment, attrition, treatment fidelity, intervention adherence and acceptability of study outcome measures. Secondary outcomes will include quality of life, functional capacity and grip strength.

**Ethics and dissemination:**

Ethical approval has been obtained from the Health Research Authority (reference number 22/PR/0390). Results of this study will be disseminated through publication in peer-reviewed articles, presentations at scientific conferences and in collaboration with patient and public involvement representatives.

**Trial registration number:**

NCT05318807.

STRENGTHS AND LIMITATIONS OF THIS STUDYFeasibility study to assess whether a future definitive study can or should be done.Inclusive research approach, tailoring interventions to a participant’s capabilities.Use of a stratified person-centred prehabilitation intervention co-designed with patient partners.Risk of potential bias owing to the lead researcher also being the clinician delivering the interventions.

## Introduction

Multimodal prehabilitation programmes incorporating nutrition, physical activity and psychological well-being are increasingly being used in surgical cancer pathways. This is in order to optimise health outcomes and enhance recovery by reducing postoperative complications^1–5^ and hospital length of stay^4 6–8^ as well as improving health reported quality of life.^9–12^ Few prehabilitation pathways exist for people who do not have surgery, despite the fact that 50%–60% of people with cancer in the UK are treated with primary, neoadjuvant or palliative chemotherapy and/or radiotherapy treatment.^13^ A small number of studies have investigated the use of prehabilitation in the neoadjuvant setting and have shown benefit in terms of postsurgical outcomes,^14–18^ but only one of these have been in lung cancer.^19^

Only a minority of people with lung cancer are eligible for surgery, with 70%–80% receiving non-surgical treatment within the UK^20^ without any prehabilitation. UK deaths from lung cancer are higher than any other cancer and treatment outcomes are poor.^21^ There is significant potential to improve outcomes for people with lung cancer and there is some evidence that prehabilitation can help. However, this has only been tested in surgical populations. A small number of studies have shown that prehabilitation before lung cancer surgery is feasible and can improve functional capacity and reduce postoperative complications. However, most of these studies focused on the benefits of exercise prehabilitation as opposed to a multimodal approach.^19 22–30^

Prehabilitation during chemotherapy, radiotherapy or immunotherapy treatment for lung cancer poses significant challenges. Treatment regimens are often prolonged and people may experience a range of toxicities, which could limit their ability to engage in prehabilitation interventions. Personalisation to person-led values and needs is therefore important, as initiation and adherence to any intervention is determined by behavioural, psychological, physiological, environmental and social factors.^31–33^ This is further supported by Bayly *et al*’s research in thoracic lung cancer^34 35^ which found that participants had varied needs, highlighting the importance of tailored support to optimise symptom control, treatment tolerance and independence.

We have co-designed a multimodal personalised prehabilitation programme with healthcare professionals and patients using a three-step participatory action research approach (see online supplemental material file 1).^36–38^ The multimodal structure of the programme is informed by the Macmillan, Royal College of Anaesthetists and National Institute of Health Cancer and Nutrition Collaboration, Research Principles and Guidance for Prehabilitation within the Management and Support of People with Cancer.^39^ This guidance incorporates nutrition, physical activity and psychological well-being using a tiered approach, tailored to whether patients need universal (applicable to anyone with cancer), targeted (applicable to those at risk of acute, chronic or latent effects of disease or treatment) or specialist (applicable to those with complex needs, severe impairment and/or disability) intervention.^39^ The first level of intervention—universal—comprises of written information and relevant signposting to support resources for all patients. If psychological, nutrition and/or physical activity needs are identified, patients then receive the appropriate intervention (targeted or specialist) according to their level of need and readiness.

10.1136/bmjopen-2023-072367.supp1Supplementary data

The personalised prehabilitation programme uses the Adversity, Restoration and Compatibility (ARC) framework^32^ to underpin a tailored and collaborative approach. The ARC framework provides a synthesised view of how people conceptualise the personal experience of living with and beyond cancer. Consistent with psychological adjustment theory,^40^ it frames this experience as an ongoing process of learning about the evolving challenge (adversity), learning how to cope effectively (restoration) and adapting one’s identity (compatibility), in parallel (see figure 1). Our programme provides a structure and process for personalising prehabilitation, which is person-centred rather than providing a purely logistical or psychometric approach. As recommend by Hickmann *et al*,^41^ such an approach could be key to empower patients to maintain progress through the prolonged, more variable context of perioncological prehabilitation.

**Figure 1 F1:**
[figure not shown]
Diagrammatic representation of the Adversity, Restoration and Compatibility (ARC) model of the experience of adjusting to living with and beyond cancer. The waves and curves reflect the fluidity and non-linear nature of the process, with the sizes reducing as one adjusts to living with and beyond cancer.

This proposed feasibility study aims to investigate whether a personalised prehabilitation programme codesigned with healthcare professionals and patients and informed by theory and evidence is feasible to implement and evaluate in clinical practice and could thereby support a future definitive study.

## Methods and analysis

Feasibility studies are particularly relevant to assess whether a future definitive study can or should be done.^42–44^ Using the Orsmond and Cohn framework for feasibility studies,^45^ this open-label, single-group study will use a mix of methods to understand the different aspects of feasibility. This will be through the inclusion of quantitative assessments, a qualitative free text questionnaire and reflective field notes to investigate areas of uncertainty regarding patient recruitment, attrition, treatment fidelity, intervention adherence and acceptability of study outcome measures. This is situated within the feasibility stage of the Medical Research Council (MRC) framework for developing and evaluating complex interventions.^46^ It will help inform if the personalised prehabilitation programme can be implemented and evaluated in clinical practice and will provide data to estimate the parameters required to design a future definitive study. The Consolidated Standards of Reporting Trials (CONSORT) reporting guideline for pilot and feasibility studies^42^ has been used for this protocol (see online supplemental material file 2).

10.1136/bmjopen-2023-072367.supp2Supplementary data

### Eligibility criteria

Inclusion criteria: Adults (≥18 years) with a diagnosis of lung cancer who are due to commence chemotherapy, radiotherapy or immunotherapy treatment. This study includes all lung cancer types and stages. People with comorbidities and those on medication will be considered eligible. Interventions will be tailored to a participant’s capabilities, thereby promoting inclusivity and optimisation of participant recruitment.

Exclusion criteria: Participants who are due to undergo lung cancer surgery, have had previous lung cancer surgery or unable to give informed consent will not be eligible for this study.

### Recruitment

Participants will be recruited from the lung cancer clinic at a single London teaching hospital via referral from the Lung Cancer Multi-Disciplinary Team. Recruitment will continue until 30 participants have been recruited or until eight months have elapsed. A pragmatic sample size of 30 participants over an eight-month recruitment period from November 2022 to June 2023 has been selected, which is feasible within the time frame of this study. This is based on 144–240 new lung cancer diagnoses per year at the study hospital, with an assumption of a 50% uptake over an eight-month period. Furthermore, it is in accordance with published guidance on recommended sample sizes for feasibility studies.^47 48^

### The personalised prehabilitation programme

All participants will be required to attend three face-to-face appointments at the study hospital for study assessments, but the interventions will be delivered using a hybrid approach; either face-to-face at the study hospital or remotely via telephone or video conferencing depending on participant preference.

The three face-to-face sessions with the lead researcher will be prior to, at week three and at week six of a participant’s oncological treatment regimen.

Following consent, participants will be guided through a set of questionnaires (as detailed below) to complete prior to their first face-to-face appointment. These questionnaires will be reviewed during the initial session, enabling the nutrition, physical activity and/or psychological well-being interventions to be stratified according to a participant’s priorities, level of readiness and expressed needs:

Cancer Behaviour Inventory (CBI) brief form: to measure self-efficacy for coping with cancer. A score of less than 50% indicates a low level of readiness, whereas a score of 50% or greater indicates a high level of readiness.^49^Patient Activation Measure (PAM): to measure a person’s knowledge, skills and confidence in managing their own health and well-being. A score of 1–2 indicates a low level of readiness, whereas a score of 3–4 indicates a high level of readiness.^50^Modified Godin leisure time exercise questionnaire: to measure activity. A score of 14 or greater demonstrates that a person is active, thereby indicating a low level of need for physical activity. Conversely, a score less than 14 demonstrates that a person is insufficiently active, thereby indicating a high level of need to optimise activity levels.^51^Patient Generated Subjective Global Assessment (PG-SGA) short form: to identify malnutrition risk. A score of less than 4 demonstrates no or minimal risk for malnutrition, thereby indicating a low level of need for nutritional support. Conversely, a score of 4 or greater demonstrates that a person is at risk of malnutrition or is malnourished, thereby indicating a high level of need for nutrition support.^52^Emotions Thermometer (ET): to evaluate levels of emotional distress. A score in any domain of less than 5 or a score of less than 4 in need for help demonstrates low levels of emotional distress, thereby indicating a low level of need. Conversely, a score of 5 or greater in any domain or a score of 4 or greater in need for help demonstrates high levels of emotional distress, thereby indicating a high level of need.^53^Patient Generated Index (PGI): to identify participant priorities.^54^

Participant needs will also be determined objectively using the six minute walk test (6MWT) to assess functional capacity and handgrip strength to assess upper body strength. Participants will undertake these functional assessments during the face-to-face sessions.

Questionnaire responses and outcomes from the functional measurements will inform the conversation with the participant about their priorities and enable interventions to be stratified according to a participant’s level of readiness and need. If a subjective (questionnaire) or objective measurement (6MWT or handgrip strength) indicates a low or high level of readiness or need, the intervention will be tailored to the individual accordingly (see figure 2A–C).

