**Figure 2 F2:**
[figure not shown]
(A–C) Examples of the models used in the personalised prehabilitation programme for psychological well-being, nutrition and physical activity.

The personalised prehabilitation programme uses a universal, targeted and specialist approach to prehabilitation interventions, in line with current guidance.^39^ All participants will receive a universal intervention comprising of written information and relevant signposting to cancer-specific nutrition, physical activity and/or psychosocial well-being support resources. If a participant identifies a psychological, nutrition and/or physical activity need, they will then receive the appropriate intervention according to their level of need and readiness (see figure 2A–C). Targeted interventions will be delivered via the use of certified apps and/or specific group activities at Maggie’s cancer centre (an independent charity that provides free cancer support, workshops and courses to help anyone affected by cancer). For example, exercise classes or nutritional educational sessions for participants undergoing treatment as well as the opportunity to attend a lung cancer support group. These group activities are run by cancer support workers or qualified instructors. Specialist interventions involve a 1:1 assessment with a registered healthcare professional such as a physiotherapist, dietitian and/or a clinical psychologist depending on a participant’s needs. The objectives of specialist intervention with the physiotherapist and dietitian are to increase physical activity and optimise dietary intake, respectively, to minimise loss of body weight and muscle mass. Specialist intervention with the physiotherapist will include tailored advice regarding resistance and aerobic exercise. In comparison, specialist intervention with the dietitian will include a full individualised nutritional assessment, taking into account anthropometric, biochemical and clinical parameters as well as undertaking a comprehensive diet history and calculation of nutritional requirements to minimise further malnutrition.

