Owing to the prolonged nature of chemotherapy, radiotherapy or immunotherapy treatment in contrast to a defined one-off target such as surgery, person-led values and needs are likely to be more variable within the context of peri-oncological prehabilitation. Throughout treatment, participants will be asked to keep a daily diary to record their symptoms, appetite, mobility and level of distress each day using a Likert scale. This will provide participants with a visual representation of their progress and help identify any adverse trends.

Participants will also receive a weekly telephone call from the lead researcher (a specialist oncology dietitian). Participants will be able to use the diary to highlight any days they found particularly good or difficult and have the opportunity to discuss these. Personalisation is central to this study and the language used during the face-to-face appointments and the weekly telephone calls has validation and compassion at its core to help build self-efficacy and sustain behaviour change.^55^ The use of the PGI to understand personal priorities is fundamental to this personalised approach. A systematic review^56^ demonstrated the large potential value of using the PGI by enabling people with cancer to participate in the decision-making process. This is key to empower people to take ownership of their own health and for the sustainability of long-term positive behaviour change and self-care.

A traffic light system with varying levels of acceptability has often been cited as a means of judging feasibility.^42 44 57–60^ Following consensus among the research team, a priori feasibility endpoints were defined using red, amber, green (RAG) criteria as shown in table 1.

**Table 1 T1:** A priori feasibility endpoints using a RAG criteria

Parameter	Red (do not proceed to a further study)	Amber (modifications± further study required)	Green (proceed to a larger study)
Recruitment rate	<30%	30%–60%	>60%
Refusal rate	>50%	30%–50%	<30%
Attrition rate	>80%	20%–80%	<20%
Intervention adherence	<30%	30%–60%	>60%

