### Primary objective and outcome measure

The primary objective is to assess the feasibility of the personalised prehabilitation programme in clinical practice by gathering data on how accessible and relevant it is for patients with lung cancer undergoing chemotherapy, radiotherapy or immunotherapy treatment. This will be addressed using the research objectives and methods of assessment outlined in table 2.

**Table 2 T2:** Research objectives and methods of assessment to investigate the feasibility of the personalised prehabilitation programme in clinical practice

Research objective	Method of assessment(s)
To estimate eligibility, recruitment, refusal and attrition rates (including the reasons why)	Descriptive statistics—number approached, eligible, recruited, refused and number who drop out and at what stage Field notes taken during the Lung Cancer Multi-Disciplinary Team Participant discussion
To assess adherence to the personalised prehabilitation interventions	Weekly telephone call—adherence to goals set
To assess the barriers and facilitators to adherence and intervention fidelity	Daily diary—symptom log Weekly telephone call Short free text questionnaire at the end of the study, analysed thematically
To evaluate acceptability of the study processes and outcome measures	Completion rates Weekly telephone call Short free text questionnaire at the end of the study, analysed thematically
To determine the ‘prehabilitation window’ (length of time between diagnosis and the start of treatment)	Descriptive statistics—date of diagnosis, date of start of treatment, date of start and finish of prehabilitation
To determine the extent to which the intervention/s are likely to have an impact on psychological well-being, nutrition and/or physical activity and quality of life	Questionnaires—change between baseline and follow-up Daily diary—symptom log Weekly telephone call Short free text questionnaire at the end of the study, analysed thematically Functional objective assessments
To determine the number of participants who require universal, targeted and specialist intervention	Questionnaires—level of need and readiness Descriptive statistics

Heterogeneity of participant characteristics is expected within the study. This will provide valuable insights into how different people experience the personalised prehabilitation programme.

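### The Emotions Thermometer low-need rule is not the complement of the high-need rule, so participants with mixed scores meet both (minor wording error)

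*Protocol article*

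**What the plan says.** The section on the personalised prehabilitation programme lists the questionnaires used to stratify participants, with a cut-off for each except the Patient Generated Index. For the Emotions Thermometer, low need is defined by: "A score in any domain of less than 5 or a score of less than 4 in need for help demonstrates low levels". The next sentence is introduced as the converse and defines high need by: "a score of 5 or greater in any domain or a score of 4 or greater in need for help demonstrates high levels".

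The neighbouring instruments have a simpler form. For the Cancer Behaviour Inventory: "A score of less than 50% indicates a low level of readiness, whereas a score of 50% or greater indicates a high level". For the Patient Activation Measure: "A score of 1–2 indicates a low level of readiness, whereas a score of 3–4 indicates a high level of readiness". The Godin questionnaire splits at 14 and the PG-SGA short form at 4, each into two levels.

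The resulting level is used. The same section says that if a measurement "indicates a low or high level of readiness or need, the intervention will be tailored to the individual accordingly". After Figure 2 it adds that participants who identify a need are allocated by it: "they will then receive the appropriate intervention according to their level of need and readiness". Table 2 has a matching descriptive objective: "To determine the number of participants who require universal, targeted and specialist intervention", assessed from the questionnaires' level of need and readiness.

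**The concern.** Two rules presented as opposites should divide participants into two groups, with nobody in both and nobody in neither. These do not. The high rule needs only one item at or above its threshold. The low rule, as printed, needs only one item below its threshold. Anyone with mixed scores therefore meets both, and the visible text has no precedence rule.

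At stake is the label given to a distressed participant. Someone with several domains well above 5 but a low need-for-help score would be low need if the low sentence were applied as printed, and high need under the next sentence. The label informs the psychological intervention and the Table 2 tier count. The article also relies on predefining parts of the programme to limit bias, because the lead researcher both delivers interventions and performs assessments (Strengths and limitations). A predefined rule that allows two answers gives less of that protection.

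The cut-offs of 5 and 4 are not in question.

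**Working it through.** The article gives no figure to reproduce, so the check is one of logic.

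**Inputs**, all from The personalised prehabilitation programme:
- Printed low: any domain < 5 OR help < 4.
- Printed high: any domain ≥ 5 OR help ≥ 4.

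**Step 1: the true complement.** By De Morgan, NOT(any domain ≥ 5 OR help ≥ 4) = (every domain < 5 AND help < 4). The printed low rule differs in two places: 'any' should be 'every', and 'or' should be 'and'.

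**Step 2: worked score sets.** Three domains plus need for help are assumed for illustration.

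| Domains; help | Printed low | Printed high | Corrected low |
|---|---|---|---|
| 7, 2, 3; 1 | yes | yes | no |
| 2, 3, 4; 6 | yes | yes | no |
| 7, 6, 8; 2 | yes | yes | no |
| 2, 3, 4; 1 | yes | no | yes |
| 7, 6, 8; 5 | no | yes | no |

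Three of five meet both printed rules. With the corrected low rule, 0 of 5 meet both and 0 of 5 meet neither.

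**Step 3: all score patterns.** The article gives neither the scale nor the number of domains, so integer scores 0–10 and k = 2 to 5 domains are assumed. There are 11^(k+1) patterns. Those meeting only the low rule number 5^k × 4 (all items below threshold). Those meeting only the high rule number 6^k × 7 (all items at or above threshold). The remainder meet both:
- k = 2: 1331 − 100 − 252 = 979, or 73.6%
- k = 3: 14641 − 500 − 1512 = 12629, or 86.3%
- k = 4: 161051 − 2500 − 9072 = 149479, or 92.8%
- k = 5: 1771561 − 12500 − 54432 = 1704629, or 96.2%

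These are shares of possible score patterns, not expected shares of patients. They show only that the overlap is not confined to a corner case of the rule.

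**Step 4: changing one word only.** Reading 'any' as 'every' in the low rule but keeping 'or' still leaves 42.0%, 38.9%, 37.5% and 36.9% of patterns (k = 2 to 5) meeting both, for example all domains below 5 with help at 6. With both words changed, 0 patterns meet both and 0 meet neither, for every k.

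**Step 5: comparators.** The Cancer Behaviour Inventory (0–100%), Patient Activation Measure (1–4), Godin (0–100, range assumed) and PG-SGA (0–36, range assumed) were checked over integer scores. Overlap and gap are 0 in each, so 0 of 4 share the problem.

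**The case against.** The strongest reply is that the intent is plain. The second sentence is offered as the converse of the first, the high rule is unambiguous, and a reader who takes low as 'not high' classifies everyone correctly. The low sentence can also be read item by item, giving a threshold for whichever domain is being scored, in which case no single item overlaps. The comparison with the other questionnaires is weak as evidence of inconsistency, because each has one score and one cut-off and so could not produce this problem. Figure 2A, which carries the psychological model, is not shown and may settle the matter.

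Consequences are also limited. Scores inform a conversation and do not allocate mechanically. Everyone receives the universal intervention. Distress is followed afterwards, since participants "record their symptoms, appetite, mobility and level of distress each day using a Likert scale" and are telephoned weekly by a lead researcher trained to recognise psychological distress.

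Most of this stands, and it fixes the weight of the point. It does not make the sentence right. Taking low as 'not high' gives the correct result only by disregarding the low sentence. The item-by-item reading leaves the participant scoring 7, 2, 3 with help 1 carrying one high label and three low ones, whereas the text goes on to use one low or high level for the measurement. A correct Figure 2A would contradict the printed sentence, not repair it. Nor is this a detail left to a fuller document: the article prints the rule and gets half of it wrong.

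**Conclusion.** The point holds as a minor wording inconsistency. The low-need sentence for the Emotions Thermometer is not the negation of the high-need sentence, and any participant with mixed scores meets both.

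The logic rests on the printed words alone. Only the illustrations depend on the assumed number of domains and, for the pattern counts, on the assumed 0–10 scale. The practical reach is the psychological need classification and one descriptive count in Table 2. None of the four red/amber/green criteria in Table 1 uses it, so the feasibility decision is unaffected, and no significance test is planned. If the high sentence is applied as printed and low is taken as its complement, no participant is misclassified. The share of participants with mixed scores cannot be obtained from the article, and no claim is made about Figure 2A.

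**What to change.** Reword the low-need sentence so that low distress, and hence low need, requires a score below 5 in all domains and a score below 4 in need for help. Leave the high-need sentence as it is. Then confirm that Figure 2A and any scoring sheet apply the same rule.

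The cost is a one-sentence correction and that check. No new data are needed and the cut-offs do not change. It is worth making before the rule is carried into the larger randomised pilot that this study is meant to inform, where other assessors may apply it as written.
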